---

## Summary

The prevalence of psychosocial problems among preschool children is already high. Early detection and treatment of emotional and behavioral problems have a positive effect on prognosis. However, currently many cases are being missed. The Invent-group strongly suggested to implement and to evaluate the test properties and impact of the Brief Infant-Toddler Social and Emotional Assessment (BITSEA) for the purpose of screening of emotional and behavioral problems among very young children (1-3 year old). The BITSEA can be applied by preventive Youth Health Care in the Netherlands (YHC; 'Jeugdgezondheidszorg 0-4 jarigen'; 'Consultatiebureaus'). YHC has a reach of over 90% of parents/children during the preschool years. We propose to validate and to evaluate the impact of the use of the BITSEA as screening tool by YHC at the routine visit of parent/children at age 24 months. The study will be done by 30 YHC-teams in the larger Rotterdam area, including both metropolitan areas with extensive and varied non-Dutch communities and non-metropolitan areas representative of the Dutch population at large. The 30 YHC-teams will include a total of net 3.000 parents/children in the study; there will be a follow-up of 12 months after the YHC-visit at age 24 months. At random 15 YHC-teams will be assigned to apply the BITSEA as a new screening tool at age 24 months (Intervention condition). The other 15 YHC-teams will apply 'usual care', i.e. application of the KIPPPPI-'Consultatie Bureau Signalerings Instrument 2-jarige' (Control condition). In the Control group, parents will also complete the BITSEA (blinded for the YHC-professionals). The Child Behavior Checklist 1,5-5 (CBCL 1,5-5) (blinded for YHC) will be used to determine concurrent validity. Bilingual versions (Dutch; Turkish/ Arabic) will be offered. Additionally, a 'clinical' sample of (net) 100 circa 2-year olds (18-30 months old) referred to Youth Care and Youth Mental Health Services will be drawn through Youth Care/Mental Care agencies in the larger Rotterdam area. Parents of these children will also complete the BITSEA and KIPPPPI-2, next to the CBCL 1,5-5. Data from the 'clinical' sample will be used to add to the validation of the screening tools. The study consists of two parts. In Part 1, test properties of the BITSEA will be determined in 2-year olds. In Part 2, the use of the BITSEA as screening tool in 2-year olds will be evaluated in comparison with the use of the KIPPPPI-2. Data collection regarding the two parts of the study overlap. All 3.000 parents/toddlers in the study will complete the BITSEA and CBCL 1,5-5 at age 24 months, and at follow-up at age 36 months (in the Control group KIPPPPI-2 will be used for screening at age 24 months); (medical) charts and registers of care will be reviewed at follow-up. Test properties of BITSEA will be described according to current standards (Part 1 of the study). Multi-level analyses will be applied in evaluating the impact of the BITSEA compared to the KIPPPPI (Part 2 of the study).

---

## Introduction

Early detection and treatment of emotional and behavioral problems in childhood may lead to considerable benefits regarding development, well-being and health (Durlak et al, 1998; Elliot et al, 2002). Given the fact that both internalizing and externalizing psychosocial problems already have a high prevalence among preschool children, it has been hypothesized that early detection and interventions should start at young age (Skovgaard et al, 2004; Carter et al, 2004; Zeijl et al, 2005). Currently however, many cases of psychosocial problems in (very) young children are being missed in the Netherlands (Reijneveld et al, 2004).

The Dutch Invent-group recently stated that collaborative efforts are needed to implement and evaluate promising ('veelbelovend'), uniform strategies by Youth Health Care (YHC; 'Jeugdgezondheidszorg') and other involved organizations to detect high-risk child-rearing situations and act upon it in a coherent, effective way (Hermanns et al, 2005). The Invent-group thoroughly assessed existing instruments to systematically screen (young) children for the presence of emotional and behavioral problems. The Invent-group identified the Brief Infant-Toddler Social and Emotional Assessment (BITSEA) as a very promising instrument to detect psychosocial problems among the youngest children, those aged 1-3 years old (Hermanns et al, 2005; page 39).

The BITSEA, a 42-item questionnaire for parents with multiple-choice answer options, is intended for early detection and screening of externalizing and internalizing problems of children aged 12 months to 3 years (Carter et al, 2004; Briggs-Gowan et al, 2004). The BITSEA scoring system provides a Problem Total Score and a Competence Total Score. A Dutch translation of the original English version is already available (Hermanns et al, 2005); Turkish and Arabic versions will be provided in this project to be applied in multi-ethnic populations. The Invent-group considers the BITSEA a potential powerful and proper screening tool for the youngest children (1-3 years), preceding the SDQ (Strengths and Difficulties Questionnaire) that is (potentially) appropriate for children at least 3 years old. The BITSEA showed, in other countries, a good sensitivity, specificity, predictive value and other satisfying psychometric properties (Briggs-Gowan et al, 2004; Hermanns et al, 2005, page 110-111). The full-length version, the ITSEA, has been applied as an epidemiological measure (not as a screening tool) in the SCP-TNO study 'Kinderen in Nederland' ('Children in the Netherlands') (Zeijl et al, 2005). Please refer to the systematic review regarding the ITSEA and BITSEA that is attached to this proposal ('Beknopte systematische zoekactie').

Despite its potential, the BITSEA has not yet been implemented and evaluated as screening tool in the setting of regular preventive Youth Health Care for preschool children that is offered to all families and has a reach of over 90%. Therefore, the Invent-group has strongly proposed to further develop and test the BITSEA in the Dutch setting and to evaluate both test properties and its potential for implementation in daily practice of Dutch Youth (Health) Care (Hermanns et al, 2005; page 39). We propose to do so in this study in the setting of YHC for preschool children ('Consultatiebureaus') in the larger Rotterdam area, including both metropolitan areas with extensive and varied non-Dutch communities and non-metropolitan areas representative of the Dutch population at large.

Dutch YHC provides an efficient framework for early detection and management of psychosocial problems in young children (Update ZonMw Programmeringsstudie, 2005). Several prior studies have shown that it is highly feasible to implement parent-completed screening tools such as the BITSEA in YHC for preschool children (Reijneveld et al, 2004; Zeijl et al, 2005; Wiefferink et al, 2006). YHC is in the process of becoming an integral part

---

of the whole chain-of-care for children and families. In the larger Rotterdam area, the setting of this study, the first ‘Centers for Youth and Families’ have already started. Furthermore, in the larger Rotterdam area, an extremely helpful regional Youth Care Registry has been implemented, promoting collaboration and quick referral between YHC and other relevant agencies (SISA/SJS registries). Also, in this area, already protocols have been implemented for the management of psychosocial problems and referral to evidence-based interventions (SJS, 2006).

In this study we will validate the BITSEA in the setting of YHC in a large varied population (part 1 of the study) and we will evaluate the impact of the use of the BITSEA as screening tool by YHC at age 2 years; the impact of the BITSEA will be compared with ‘usual care’, which in the Rotterdam area is application of the KIPPPI-‘Consultatie Bureau Signalerings Instrument 2-jarige’ (see ‘Strategy’) (part 2 of the study).

## **Objective**

The objective of this study is to validate the Brief Infant-Toddler Social and Emotional Assessment (BITSEA) (Part 1 of the study) and to evaluate the impact of the use of the BITSEA as screening tool by preventive Youth Health Care (YHC; ‘Jeugdgezondheidszorg’) at age 24 months, compared to ‘usual care’, i.e. application of the KIPPPI-‘Consultatie Bureau Signalerings Instrument 2-jarige’ (Part 2 of the study). In the study, the Child Behavior Checklist 1,5-5 (CBCL 1,5-5) will be used to determine concurrent validity of the BITSEA. Furthermore, in the study, data of a ‘clinical’ sample will be used to add to the validation of the BITSEA. In Part 2 of the study follow-up measures at age 36 months will be used.

## Research questions:

### **PART 1 OF THE STUDY: ‘TEST PROPERTIES’**

1. What are the sensitivity, specificity, predictive value of test results, and other psychometric test properties (including reliability, factorial validity, concurrent and discriminative validity) of the BITSEA?

### **PART 2 OF THE STUDY: ‘BITSEA AS SCREENING TOOL’**

2. What is the outcome at 12-months follow-up of the use of the BITSEA in YHC centers that apply it compared to YHC centers that apply the KIPPPI-‘Consultatie Bureau Signalerings Instrument 2-jarige’ (‘usual care’) in terms of (a) emotional and behavioral problems at follow-up, and (b) delivery of care and interventions (number, type, adherence, rapidity)?

3. What is the feasibility of the use of the BITSEA as screening tool according to professionals and parents?

4. What are the costs of the use of the BITSEA per detected case and what is the ratio between costs and effects of BITSEA use in terms of improvement of indicators of psychosocial health at follow-up compared to usual care?

We will explore test properties, outcomes and process characteristics for subgroups non-Dutch children.

---

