The theoretical model applied in this study, is the model of screening for abnormalities, followed by referral, diagnosis and early treatment if indicated (see Mackenbach et al, 2008, page 240-253). This model of screening has been developed in the medical setting, e.g. for early detection and treatment of tuberculosis (mid 20th century) or early detection and treatment of specific cancers (late 20th century). Late 20th century, early 21st century this model was transferred to the early detection, referral, diagnosis and treatment of emotional and behavioral problems (and even risks for the development of such problems) in childhood (Hermanns et al, 2005).

The underlying assumption of the model of screening is that early detection, diagnosis and treatment (i.e. earlier than would have happened in the ‘natural course of events’, i.e. without the screening procedure) results in outcomes that are better compared to outcomes in the case of no screening. However, the model of screening acknowledges that depending on the condition for which is being screened, the screening procedure and the setting, a screening procedure may be ineffective or may even be harmful. This is reflected in a quote by Sir Muir Gray ‘all screening programs do harm; some do good as well’ (cited by Mackenbach et al, 2008, page 242). The circumstances that are related to the (potential) outcomes of a screening are summarized in 10 criteria for effective screening that were proposed by Wilson and Jungner (cited by Mackenbach et al, 2008, page 250):

- 
1. The problem/disease should present a public health problem (i.e. a relevant problem at societal level).
  2. An acceptable and effective treatment should be available.
  3. Ample facilities for further diagnosis and treatment should be available.
  4. The problem/disease should have a clear 'latent' phase (i.e. a - hypothetical, ideal - screening test should be helpful to discover a problem/disease that otherwise would have remained unseen/undiagnosed).
  5. The test properties (among which sensitivity, specificity, predictive value of test results) should be adequate.
  6. The screening test should be acceptable for the population.
  7. The natural course of the problem/disease should be known (i.e. the course of the problem/disease in the absence of screening).
  8. Protocols regarding criteria for referral and further diagnosis, and criteria for diagnosis and treatment should be available.

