  9. The costs of the whole screening procedure (including referral, diagnosis, and treatment) should be acceptable in the whole context of (health) care.
  10. The screening process should be well-organized and should be embedded in a continuous program (i.e. not an ad-hoc procedure).

Part 1 and Part 2 of this study will clearly contribute to the empirical knowledge needed to decide on future implementation of screening for emotional and behavioral problems in 2-year olds by using the BITSEA in preventive Youth Health Care in the Netherlands, given the 10 criteria of Wilson and Jungner.

Adequate test properties of the BITSEA (criterion 5) have been established in the U.S.. This study will contribute to the knowledge needed to decide on the plausibility of the BITSEA screening in the Netherlands by evaluating the test properties of the BITSEA in the context of day-to-day practice of preventive Youth Health Care in the Netherlands.

Hypotheses applied in Part 2 of the study:

We hypothesize that use of the BITSEA as screening tool compared to KIPPPI-2, results in more appropriate and timely care; and that fewer problems indicated by the CBCL 1,5-5 will be present at 1 year follow-up in the BITSEA group (Intervention condition) compared to the KIPPPI-2 group (Control condition).

We also hypothesize the (relative) costs of the use of the BITSEA to be lower than the costs of the KIPPPI-2 as screening tool.

---

|                                        |
|----------------------------------------|
| PART 1 OF THE STUDY: 'TEST PROPERTIES' |
|----------------------------------------|

In the Part 1 of the study test properties, including psychometric characteristics, sensitivity, specificity and predictive value of the BITSEA will be studied (Research question 1).

Please refer to the attached Annex with a schematic overview of study populations and design of Part 1 and Part 2 of the study. Please also refer to the attached Annex with a systematic review of the literature on the BITSEA, including a description of the instrument. (see Proposal zomnw)

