### ***1.4 Data analysis***

Test properties of the BITSEA will be described, including internal consistency, inter-rater reliability, factorial validity, concurrent validity with the CBCL 1,5-5, and discriminative validity (BITSEA results compared to professional findings). Receiver Operating Characteristic (ROC) curves for all possible cut-off points will be made available by using results of the ‘clinical’ sample. See Mackenbach et al (2008), page 240-253 for description of the test properties and procedures to evaluate the BITSEA as screening tool.

Two criteria will be used in this analysis: (a) a ‘clinical score’ on the CBCL 1,5-5; and (b) referral to Youth Care/Child Mental Health Care (and additionally other professional diagnoses by YHC-professionals or Youth Care/Mental Health Care professionals).

Normative data and cut-offs will be produced based on the total community sample. All test results will be explored and described for subgroups of children from ethnic minorities.

---

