#### **Outcomes**

- CBCL 1,5-5 at baseline and 12-month follow-up (CBCL 1,5-5 scores are considered the primary outcomes)
- BITSEA at baseline and 12-month follow-up
- YHC-professional problem diagnosis and treatment/referral decisions at baseline and during follow-up (Reijneveld et al, 2004; Zeijl et al, 2005)
- Entries in the regional Youth Care Registries (SISA/SJS) at baseline and during follow-up (SJS, 2006)
- Child health-related quality of life (General health perceptions subscale of the ITQOL; Raat et al, 2006)

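### Part 2 hypothesises more appropriate care and warns of harm, but none of its care outcomes is tied to need, so better detection and over-referral cannot be told apart between arms

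*Protocol*

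**What the plan says.** The Study Design section adopts the screening model and accepts that "a screening procedure may be ineffective or may even be harmful". Its hypothesis for Part 2 is that using the BITSEA instead of the KIPPPI-2 "results in more appropriate and timely care", with fewer CBCL problems one year later.

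The care outcomes are set in two places. Research question 2(b) lists "delivery of care and interventions (number, type, adherence, rapidity". Section 2.3 lists "YHC-professional problem diagnosis and treatment/referral decisions at baseline and during follow-up", and separately the entries in the regional registries. Section 2.3 also states that "CBCL 1,5-5 scores are considered the primary outcomes", so care is not the primary outcome.

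Question 4 opens with "What are the costs of the use of the BITSEA per detected case" and goes on to ask for the ratio of costs to effects on psychosocial health at follow-up.

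Section 2.4 compares the arms on each outcome with multilevel linear or logistic models. The only interactions it names are with gender and ethnic background.

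Part 1 asks "What are the sensitivity, specificity, predictive value of test results, and other psychometric test properties" of the BITSEA. Section 1.4 says: "Two criteria will be used in this analysis: (a) a ‘clinical score’ on the CBCL 1,5-5; and (b) referral to Youth Care/Child Mental Health Care".

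**The concern.** Care can only be called appropriate relative to need. A referral of a child with a problem and a referral of a child without one enter question 2(b) and section 2.3 in the same way. The harm that a screening programme most plausibly does, through false-positive labels and referrals, has no outcome of its own, and neither has the missed case.

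If the BITSEA arm shows more diagnoses, more referrals or faster care, the protocol gives no means of saying whether more affected children were reached or more unaffected children were referred. The Relevance section says the results will inform decisions on nationwide implementation, so the distinction matters. The cost question has the same gap, because a detected case is not defined as a confirmed one.

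**Working it through.** The claim concerns what the outcomes measure. The plan states no figure on this point, so there is none to reproduce.

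**Step 1. Is any Part 2 care measure linked to need?**

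| Place | Measure | Linked to need? |
|---|---|---|
| Question 2(b) | number, type, adherence, rapidity of care | no |
| 2.3 Outcomes | diagnosis, treatment and referral decisions | no |
| 2.3 Outcomes | registry entries | no |
| 2.2 and 2.3 Process measures | satisfaction (including with referral), adherence, time and costs | no |
| 2.4 | arm effect; interactions by gender and ethnicity | no term for need |
| 2.5 | subgroup with problems at baseline | yes, but the outcome is the CBCL score, not care |
| Question 4 | cost per detected case | confirmation not required |

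**Step 2. Does Part 1 fill the gap?** Only in part.
- It judges the BITSEA score, whereas care follows a professional's decision that also draws on other observations (2.2).
- It plans no comparison between arms. In the community sample the KIPPPI-2 is available in the Control group only (1.3).
- One of its two criteria is referral, which cannot reveal over-referral.

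**Step 3. Illustration of what an undivided count hides.** Inputs: N = 1,500 per arm (inclusion schedule annex); prevalence 10% (the figure for problems at baseline in 2.5); sensitivity and flag rate are assumptions. Flagging stands in for any undivided care count.

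Formulas: true positives TP = N × prevalence × sensitivity; false positives FP = flagged − TP; PPV = TP / flagged.

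(a) Sensitivity fixed at 0.80, so TP = 1,500 × 0.10 × 0.80 = 120:

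| Flagged | n flagged | TP | FP | PPV |
|---|---|---|---|---|
| 10% | 150 | 120 | 30 | 0.80 |
| 20% | 300 | 120 | 180 | 0.40 |
| 30% | 450 | 120 | 330 | 0.27 |

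The count doubles or triples with no extra case found. At 20% flagged, over prevalence 5% to 15% and sensitivity 0.6 to 0.8, PPV runs from 45/300 = 0.15 to 180/300 = 0.60.

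(b) Flag rate fixed at 10% in both arms, as the p90 rule in 2.2 would suggest: 150 flagged and 150 children with problems. At sensitivity 0.40, TP = 60, FP = 90 and 90 cases are missed. At sensitivity 0.80, TP = 120, FP = 30 and 30 cases are missed. Two arms at these extremes differ twofold in cases found, yet both report 150 flagged children. The undivided count can therefore also hide a real gain.

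**Step 4. Are the data for a need-based comparison planned?** Yes. The 24-month CBCL is completed in both arms and is not used in the routine assessment (2.2). Decisions and registry entries are retrieved in both arms. Sections 1.2 and 2.2 call the additional questionnaire anonymous, but 2.4 adjusts for baseline values and 2.5 uses a subgroup defined at baseline. Both need linkage to the child.

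**The case against.** The strongest reply is that the protocol does not rest its case on care counts. The primary outcome is the CBCL score, so over-referral without gain should appear as more care and no CBCL benefit. Part 1 would expose a low specificity or predictive value of the BITSEA. The p90 rule applies in both arms, so a more liberal screen is not built in. Cross-tabulating care by CBCL status is the kind of detail an analysis plan may hold, and that plan is not shown.

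Much of this stands as mitigation. It does not close the gap:
- A mean CBCL score per arm does not show which children received care.
- Part 1 compares no arms.
- Equal flag rates still hide different detection, as illustration (b) shows.
- An analysis plan may define terms, but the hypothesis, the outcome list and the cost unit are all in this protocol.

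Three stronger readings are tempting, and the document does not support them.
- A reader might infer that the protocol measures only the amount and speed of care. It also lists type and adherence, and it collects satisfaction with referral. None of these measures need.
- A reader might infer that over-referral would be scored as a benefit. The protocol gives no direction for the counts, and its hypothesis is more appropriate and timely care, not more care.
- A reader might infer that over-referral would make the BITSEA look cheaper. That holds only if total cost stays the same and every flagged child counts as detected. Study Design treats referral, diagnosis and treatment as part of the cost of screening, and question 4 also asks for a ratio of costs to health effects.

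**Conclusion.** The concern holds in limited form. Part 2 hypothesises more appropriate care and acknowledges possible harm, but no care outcome or planned analysis relates care to need. Followed as written, it cannot test the appropriateness half of its care hypothesis, and a difference in care between arms could not be told apart from over-referral. Cost per detected case is open to the same ambiguity.

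The primary CBCL comparison is unaffected. The size cannot be fixed from the document: the illustrations rest on the 10% prevalence in 2.5 and on assumed sensitivities and flag rates. They show what a count can conceal, not what the trial will find. The point is worth acting on because the remedy is cheap.

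**What to change.** 1. In 2.3 and 2.4, keep the planned care outcomes and add two secondary arm comparisons with the planned multilevel logistic model: (1) problem diagnosis or referral among children with a non-clinical 24-month CBCL; (2) no diagnosis or follow-up care among children with a clinical-range 24-month CBCL.
2. In question 4, report cost per CBCL-confirmed detected case, defined identically in both arms, beside cost per flagged child.
3. In 1.2 and 2.2, state that the 24-month questionnaire is coded and linkable to the child rather than anonymous. Also state whether parents complete it before the visit, since it defines the strata.

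The 36-month CBCL change among labelled children should not be added as an arm comparison. Being labelled happens after randomisation, so the groups compared would no longer be randomised ones.

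The cost is wording and analysis time, with no new measurement. There are two limits.
- **Criterion.** The CBCL is parent-reported and provisional. Care given to a child with a non-clinical score is not CBCL-confirmed, which is weaker than unnecessary. The criterion may also favour whichever instrument lies closer to it.
- **Precision.** Assume the ICC of 0.10 from 2.5 also applies to care decisions. With 15 teams per arm and 10% of children in the clinical range, the non-clinical stratum has 1,350 children per arm (90 per team), design effect 1 + 89 × 0.10 = 9.9 and effective n = 1,350 / 9.9 ≈ 136. At a 10% referral rate the 95% half-width for the difference is 1.96 × √(2 × 0.10 × 0.90 / 136) ≈ 0.07. The clinical stratum has 150 per arm (10 per team), design effect 1.9 and effective n ≈ 79. At 50% the half-width is 1.96 × √(2 × 0.50 × 0.50 / 79) ≈ 0.16. Both comparisons should be reported as estimates with intervals.

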### **2.4 Data analysis**

Multilevel analyses will be applied to allow for dependency between the individual measurements within the randomized YHC-teams (Campbell et al, 2004; Twisk, 2006). Multilevel linear regression analyses will be conducted for the continuous outcome variables with group (intervention or control) as independent variable and baseline values and potential confounders as covariates. Multilevel logistic regression will be performed in case of dichotomous outcome variables. Interaction effects by gender and ethnic background will be explored by introducing an interaction term into the regression analyses (Twisk, 2006).

Adherence to and satisfaction with the distinct elements of the early detection procedure by parents and professionals will be described.

Costs and effects will be evaluated for the purpose of a cost-benefit analysis.

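### Rapidity of care is a stated outcome, but neither model named in section 2.4 handles a censored time; analysed as a continuous time, it would be compared only among children who received care

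*Protocol*

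**What the plan says.** The research questions for Part 2 make rapidity one of four aspects of care delivery: "delivery of care and interventions (number, type, adherence, rapidity". The Part 2 hypotheses, under Study Design, give it a direction: use of the BITSEA rather than the KIPPPI-2 "results in more appropriate and timely care". The same paragraphs also hypothesise fewer CBCL problems and lower costs, so timeliness is one part of one of three hypotheses.

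Section 2.3 states that "CBCL 1,5-5 scores are considered the primary outcomes". The care outcomes it lists are "YHC-professional problem diagnosis and treatment/referral decisions at baseline and during follow-up" and "Entries in the regional Youth Care Registries (SISA/SJS) at baseline and during follow-up". It does not say when the clock for rapidity starts, which event stops it, or how a child without care is counted.

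Section 2.4 gives a general rule by type of outcome: "Multilevel linear regression analyses will be conducted for the continuous outcome variables with group (intervention or control) as independent variable", adjusted for baseline values and potential confounders, and "Multilevel logistic regression will be performed in case of dichotomous outcome variables". No other type of outcome model is named.

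**The concern.** The natural measure of rapidity is the time from the 24-month visit to first care. Follow-up ends 12 months later, so a child who has had no care by then has a censored time, not a value. A linear model either drops that child or needs an invented value.

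Dropping such children leaves only recipients of care. Who becomes a recipient depends partly on what the screening tool flags at the visit, and the tool is what was randomised. The two groups of recipients need not be comparable. If the BITSEA leads to care for additional, milder children who are seen later, the mean time in its arm could lengthen although no child was served later than before. If the BITSEA simply raises the rate of care, the mean among recipients hardly moves. Either way, the hypothesis on timely care could be answered wrongly.

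**Working it through.** The protocol gives no rate of care, hazard ratio or power for rapidity, so there is no stated figure to reproduce. The calculation below only tests the mechanism.

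**Inputs from the protocol.** Follow-up of 12 months (2.1); 2,100 children with complete data, equally divided, so 1,050 per arm, and alpha 0.05 (2.5).

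**Assumptions.** Constant rate of first care; share of control children with care by 12 months p₀ = 5%, 10%, 20% or 40%; hazard ratio (HR) 1.5 or 2.0; two-sided test; no clustering at first.

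**Formulas.** With T = 12:
- Control rate λ₀ = −ln(1 − p₀)/T. The other arm has λ₁ = HR × λ₀ and p₁ = 1 − (1 − p₀)^HR.
- Mean time among recipients = 1/λ − T·exp(−λT)/(1 − exp(−λT)).
- Recipients-only power: normal approximation with 1,050·p₀ and 1,050·p₁ children.
- Time-to-event power (Schoenfeld): Φ(√(E/4)·ln HR − 1.96), with E = 1,050·(p₀ + p₁) events.
- Care by 12 months, yes or no: two-proportion test in all children.

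**One case in full.** Take p₀ = 10% and HR = 2.
- λ₀ = 0.1054/12 = 0.00878 and p₁ = 1 − 0.9² = 19%.
- The recipient means are 5.89 and 5.79 months, a difference of about 0.105.
- Recipients number 105 and 199.5, each with SD about 3.46, so SE = √(3.46²/105 + 3.46²/199.5) ≈ 0.417. The ratio is 0.105/0.417 ≈ 0.25, and power is about 6%.
- E = 304.5, so √(304.5/4) × 0.693 − 1.96 ≈ 4.09, and power exceeds 99%.

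| Control care rate | HR | Other arm | Mean months, recipients | Power: recipients only | Power: time to event, all | Power: care by 12 months, all |
|---|---|---|---|---|---|---|
| 5% | 1.5 | 7.4% | 5.95 vs 5.92 | 5.0% | 64% | 63% |
| 5% | 2.0 | 9.8% | 5.95 vs 5.90 | 5.1% | 99% | 99% |
| 10% | 1.5 | 14.6% | 5.89 vs 5.84 | 5.2% | 90% | 90% |
| 10% | 2.0 | 19.0% | 5.89 vs 5.79 | 5.7% | >99% | >99% |
| 20% | 1.5 | 28.4% | 5.78 vs 5.67 | 6.5% | >99% | >99% |
| 20% | 2.0 | 36.0% | 5.78 vs 5.56 | 11.6% | >99% | >99% |
| 40% | 1.5 | 53.5% | 5.49 vs 5.24 | 20.5% | >99% | >99% |
| 40% | 2.0 | 64.0% | 5.49 vs 5.00 | 64.5% | >99% | >99% |

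**Clustering.** Section 2.5 assumes an intraclass correlation of 0.10. With 2,100/30 = 70 children per team, the design effect is 1 + 69 × 0.10 = 7.9. If that applied to care, time-to-event power would fall to 58% in the worked case (55% for care by 12 months), and would run from 13% to 85% over control rates of 5% to 20%. The recipients-only comparison would not gain from clustering. The protocol gives no intraclass correlation for care itself.

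**The case against.** The strongest reply is that the protocol nowhere commits to a recipients-only comparison. Rapidity is one undefined word in a bracket, and section 2.4 is a general rule that does not mention it. A reader might infer that the plan will compare times only among children who received care. The documents do not say so, and that stronger reading is not supported. Decisions and registry entries could be coded as yes or no in all children and analysed with the logistic model that section 2.4 names.

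A reader might also infer that the plan would miss a higher rate of care altogether. It need not: number and type of care stand in the same research question, and the last column of the table shows that a logistic analysis of care by 12 months detects these effects almost as well as a time-to-event analysis.

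That reply holds for uptake. It does not settle speed. The two analyses agree in the table because, under a constant rate, more care and faster care go together. If both arms reached the same proportion by 12 months and one got there months earlier, the 12-month logistic model would show nothing, although that is exactly a difference in rapidity. An earlier cut-off would capture it, but the protocol sets none.

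It is also fair that a statistical analysis plan, not shown, may refine models for secondary outcomes. But the protocol does state a model rule, and the rule does not fit one of its own outcomes. Finally, the constant rate is doubtful, because referral decisions are recorded at the 24-month visit and care may cluster early. The powers are therefore illustrative, and the recipients-only loss shrinks where care is common.

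**Conclusion.** The point holds in conditional form. Rapidity is a stated outcome with a directional hypothesis, and neither named model handles a time that is censored for children without care. If rapidity is treated as a continuous time, the comparison rests on a group selected after randomisation. On the assumed rates (5% to 20% in control, hazard ratio 1.5 to 2.0), it would have about 5% to 12% power where a time-to-event analysis of all children has 64% to over 99%, before clustering. At 40% and a hazard ratio of 2 it reaches about 65%. All of this rests on assumed care rates and a constant rate of first care. The selection problem itself does not depend on those figures. Because the CBCL scores are primary, this is an improvement to a secondary analysis and does not threaten the main result.

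**What to change.** In section 2.4, define rapidity as time from the 24-month visit to first registered care or referral, in all included children, censored at 36 months or at loss to follow-up. Analyse it in one of two ways, named in advance:

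- a time-to-event model that allows for YHC team, by shared frailty or team-robust variance; or
- a multilevel logistic model for care by a prespecified early time point, which stays within the models already named.

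Care by 12 months can be kept as the measure of uptake, reported as such. A count model for the number of care contacts is optional and not part of this point.

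The cost is small. Sections 2.2 and 2.3 already plan retrieval of decisions, record entries and registry entries. Their dates must be extracted as well; the protocol does not state that dates are recorded, though this is likely and should be confirmed.
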